## Data analysis

Generalised Estimating Equations (GEE) will be used to analyse the two data points, including variable interactions. GEE can account for repeated measures as well as the potential problem that the primary outcome variable (RT) may not be normally distributed (although it will be continuous). Using GEE, the effects of the predictors on RT can be modelled under different circumstances, and the interrelationships between predictors can also be investigated. Significance testing will be undertaken at the *p* < 0.05 level.

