### Sample size

A power analysis calculation was based on reaction time (RT) measures in Silverstein et al. [34], who reported a mean RT of 2134.1 ms (SD = 856.6 ms) pre-treatment and 1403.6 ms (SD = 462.3 ms) post-treatment for meditators, and 1865.1 ms (SD = 800.4 ms) pre-treatment and 1893 ms (SD = 780.6 ms) post-treatment for controls. This gave a treatment-by-time partial eta-squared of 0.15, with a *p* value of 0.03. Using the same partial eta-squared for the three group, two time point studies, with alpha = 0.05 and 80% power, a minimum of 54 participants would be required in total (across all group conditions). This equates to a minimum of 18 participants per group to detect the main effect in the spatial cueing task. (regarding the stop/signal task, Verbruggen and De Houwer [35] detected effects in a single group with a sample size of 23 participants.) We will aim for 70 participants in total, assuming a drop-out buffer of approximately 5–10 participants. This will allow 20+ participants in each group.

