## Variables

### Predictor variables (both tasks)

Group membership ([interoception groups] vs. [control];Data point/time (baseline vs. follow-up);Interoceptive accuracy/sensitivity (continuous measure);Interoceptive sensibility (continuous measure);Interoceptive metacognitive awareness (continuous measure);Heart phase ([systole] vs. [diastole]);Valence of emotional stimuli ([positive: *stop/signal task only*] vs. [negative] vs. [neutral]).

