### Spatial cueing task

One of the interoception groups will show significantly faster reaction times (RTs) and greater response frequency to emotional stimuli regardless of cue type compared with each of the other groups after baseline; plus, there will be a greater change between baseline and follow-up. Each of the interoception groups separately and combined will show significant differences from the control group.One set of cues for the same group (i.e. the interoception group in (1)) will facilitate significantly faster RTs and greater response frequency. This set will match the target area of the body for that group (i.e. a chest cue for the cardioception group; a lower abdomen cue for the gastroception group). The “matching” cue for the other interoception group will not facilitate faster RTs or greater response frequency. If any cue facilitates faster RTs or greater response frequency for the other groups, it will be the same cue that facilitates for the interoception group in (1).This same group will display greater within-group coherence in the location of the body indicated to be active during trials compared with the other groups after baseline. It will also show the greatest change between baseline and follow-up compared with the other groups.This same group will report greater intensity compared with the other groups after baseline. It will also show the greatest change between baseline and follow-up compared with the other groups. The interoception groups combined will report greater intensity than the control group.This same group will show greater heart rate deceleration after baseline following the presentation of emotional stimuli compared with the other groups; both interoceptive groups will show greater heart rate deceleration than the control group.

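### Baseline-adjusted group contrasts would be more precise than the planned group-by-time contrast: a 39% variance cut if the pre-post correlation is 0.22, 10% if it is 0.8

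*Protocol article*

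**What the plan says.** The Data analysis section gives the method in one sentence: "Generalised Estimating Equations (GEE) will be used to analyse the two data points, including variable interactions". It adds "Significance testing will be undertaken at the *p* < 0.05 level". Under Variables, reaction time (RT) is the primary outcome for both tasks. The predictors for both tasks include group and "Data point/time (baseline vs. follow-up"; baseline RT is not listed as a covariate, and no constraint on baseline means is described.

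The Sample size section takes its effect from a cited meditation study: "This gave a treatment-by-time partial eta-squared of 0.15", with a p value of 0.03. It carries this value to three groups and two time points: "with alpha = 0.05 and 80% power, a minimum of 54 participants would be required in total". The recruitment target is 70, with 5 to 10 expected to drop out.

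The first spatial cueing hypothesis has two parts. One compares groups after baseline; the other reads "plus, there will be a greater change between baseline and follow-up". The stop/signal hypothesis has the same two parts. Hypothesis 8 is about improvement between the visits on the self-report scales.

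Under Randomisation, allocation is 1:1:1. It is generated once recruitment and scheduling are complete, and participants learn it only after baseline data collection, from sealed notes.

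**The concern.** In a randomised trial any baseline difference between groups is chance. A group-by-time contrast nevertheless subtracts the observed baseline difference in full, and so carries its noise into the estimate. How much this costs depends on the correlation r between a person's baseline and follow-up values. When r is below 0.5, a raw change score is noisier than the follow-up value alone. The protocol does not state r, but the figures it quotes for sample size point to a low value. With about 20 participants per group, chance baseline imbalance is not negligible. The information needed to remove it is collected anyway.

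**Working it through.** **1. What the planned term estimates.** With group, time and their interaction in the model, an identity link and complete data on person-level RT, the fitted group-by-time means are the sample means under any working correlation. The interaction is therefore the difference in mean raw change. Choosing a working correlation does not recover the precision that baseline adjustment gives.

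**2. The plan's sample size.** f² = 0.15/(1 − 0.15) = 0.1765, for a three-group test on change (2 df), alpha 0.05.
- Large-sample chi-square, noncentrality f²N: power 79.5% at N = 54; 80% is reached at N = 55. This essentially reproduces the stated 54.
- Exact noncentral F: power 77% at N = 54; 80% is reached at N = 58. At the 60 to 65 expected completers (70 − 10 to 70 − 5), power is 82% to 85%.

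**3. The correlation implied by the planning figures.** Inputs from the Sample size section: "mean RT of 2134.1 ms (SD = 856.6 ms) pre-treatment and 1403.6 ms (SD = 462.3 ms) post-treatment for meditators"; for controls, 1865.1 (SD 800.4) to 1893 (SD 780.6) ms.
- Difference in change: (1403.6 − 2134.1) − (1893 − 1865.1) = −730.5 − 27.9 = −758.4 ms.
- The arm sizes are not given, so assume two equal arms of 16: 30 error df, F = 0.1765 × 30 = 5.29, p = 0.0285, which agrees with the quoted 0.03.
- Standard error = 758.4/√5.29 = 329.6 ms. SD of change = 329.6 × √(16/2) = 932 ms.
- Average over arms of SDpre² + SDpost² = 1,098,731. Average of 2 × SDpre × SDpost = 1,020,798.
- r = (1,098,731 − 932.3²)/1,020,798 = 0.22.

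Rounding of eta-squared and p gives r from 0.19 to 0.26; a 40:60 split of the arms gives up to 0.28.

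**4. Variances, for common SD σ.**
- Raw change: 2σ²(1 − r)
- Follow-up alone: σ²
- Follow-up adjusted for baseline: σ²(1 − r²)

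Adjusted over change is (1 + r)/2, a cut of (1 − r)/2. Adjusted over follow-up alone is 1 − r², a cut of r². At r = 0.22 the three variances are 1.56σ², 1.00σ² and 0.95σ².

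**5. Power for the plan's effect.** Exact F with one covariate, f² divided by (1 + r)/2.

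| Analysis | Cut against change | Cut against follow-up only | Power, N = 54 | Power, N = 60 | Power, N = 65 |
|---|---|---|---|---|---|
| Raw change | – | – | 77% | 82% | 85% |
| Adjusted, r = 0.22 | 39% | 5% | 94% | 96% | 97% |
| Adjusted, r = 0.5 | 25% | 25% | 88% | 92% | 94% |
| Adjusted, r = 0.7 | 15% | 49% | 84% | 88% | 90% |
| Adjusted, r = 0.8 | 10% | 64% | 81% | 86% | 89% |

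The planning SDs are unequal. Using them in place of a common SD gives a cut against change of about 40% (control-arm SDs) to 55% (SDs pooled over arms), so the common-SD 39% is the cautious figure.

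**The case against.** The strongest reply is that nothing here is an error. Under randomisation the group-by-time contrast is unbiased, controls the type I error, answers the change hypotheses as worded and matches the effect used for sample size. That stands: this is a matter of efficiency.

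Second, the article does not write out the model or link, and a statistical analysis plan that is not shown could add a baseline covariate or a baseline constraint without contradicting anything here. That also stands. But the stated predictors, hypotheses and sample size all point to the unadjusted interaction.

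Third, r = 0.22 comes from another study's task and an assumed arm split. This trial has 248 cueing trials and 480 stop/signal trials (8 × 60) per visit, so its person-level RT may correlate more strongly. This stands, and is why the gain is given as a range. No correlation is available for the questionnaires or the interoception tasks, so the size of their gain is unknown.

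Fourth, the hypotheses also contain a follow-up comparison, for which adjustment gains only about 5% at r = 0.22. This stands too; 39% is not the gain for every primary comparison.

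A reader might go further and infer from the planning study's 269 ms baseline gap (2134.1 − 1865.1) that its effect is inflated and the change analysis badly underpowered. The documents do not support this. They do not say whether that study was randomised, so the gap cannot be assigned to chance, and turning its two-group difference into a three-group effect needs an assumption about the third group. For the effect the plan adopts, the change test already exceeds 80% power at 60 to 65 completers. Nor can the gain be said to dwarf the drop-out allowance, since that depends on the unknown r. Finally, allocation is generated before the baseline visit, so baseline does not strictly precede it. The case for adjustment rests on randomisation and on concealment until baseline is complete.

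**Conclusion.** The point holds as a precision improvement that needs no new data. The contrast on which the trial is sized has a larger variance than one adjusted for baseline, by an amount that depends on r: the cut is 39% at the inferred 0.22 and 10% at 0.8. Adjustment does not lose precision in large samples at any r. The planned analysis is neither invalid nor underpowered for its own effect; at the expected number of completers, adjustment adds between about 4 and 14 percentage points of power over the range r = 0.8 to 0.22.

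The figures assume person-level outcomes, an identity link, complete pairs and a common SD. The value 0.22 also assumes roughly equal arms in the planning study and that its correlation carries over to this trial. A different link would make the percentages approximate.

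**What to change.** For person-level RT and the other continuous outcomes measured at both visits (DERS, ERS, SF-36 sub-scales, MAIA, heartbeat and water load tasks), state that the primary group contrast is the difference at follow-up adjusted for the participant's own baseline value. Equivalently, keep both time points in the model and constrain the three group means to be equal at baseline. Report unadjusted change descriptively. This also gives one primary contrast where the hypotheses now offer a follow-up comparison and a change comparison.

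The cost is a short addition to the analysis text, with two choices to record. The baseline RT summary must be named (overall or cue-specific), because cueing-task RTs exist only where a bodily change was reported. The statement in hypothesis 7 about the groups at baseline becomes descriptive. The choice should be fixed before outcomes are examined by group; if that has already happened, the adjusted analysis should be reported as a labelled additional analysis.

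### If the planned GEE tests use the usual uncorrected sandwich Wald chi-square, 20 participants per group gives a type I error of about 7% (group-by-time) to 10% (three-level cue interaction) instead of 5%

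*Protocol article*

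**What the plan says.** The Data analysis section of the protocol article states: "Generalised Estimating Equations (GEE) will be used to analyse the two data points, including variable interactions". Its reason is that "GEE can account for repeated measures as well as the potential problem that the primary outcome variable (RT) may not be normally distributed", and it closes with "Significance testing will be undertaken at the *p* < 0.05 level". It does not say whether the standard errors are robust or model-based, what reference distribution is used, or whether a small-sample correction applies.

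The Sample size section sets the scale. "We will aim for 70 participants in total, assuming a drop-out buffer of approximately 5–10 participants", and "This will allow 20+ participants in each group". The stated minimum is 54 in total, 18 per group.

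The Variables section lists group as the interoception groups against control. It lists cue position either as three body areas or as a body part cued against none cued. The Hypotheses section also compares the three groups with one another.

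**The concern.** GEE is valid without normality, and with a mis-specified working correlation, because the sandwich variance converges as the number of independent clusters grows. Here the cluster is the participant. The 248 spatial cueing trials that each person completes do not add clusters. With about 20 people per group, the uncorrected sandwich is biased downwards, and a chi-square reference ignores the uncertainty in the estimated variance. Both errors push p values down, and the effect grows with the degrees of freedom of the test.

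At stake is the false-positive rate. An omnibus test of whether cue effects change differently across groups bears on the localisation claim, and it would be affected more than the plain group-by-time test.

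**Working it through.** **Inputs.** Alpha 0.05 and GEE with interactions (Data analysis). Three groups at 1:1:1 (Randomisation). Two time points (Design). Partial eta-squared 0.15, minimum 54, target 70 with 5–10 lost (Sample size). Completers: 70 − 10 = 60 to 70 − 5 = 65, so 20 to about 22 per group. The cases run below are 18 (the minimum), 20, and 23 (70/3, no loss).

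**The plan's own figure.** "This gave a treatment-by-time partial eta-squared of 0.15, with a *p* value of 0.03" gives f² = 0.15/0.85 = 0.1765. For a 2-df test with N = 54, λ = 54 × 0.1765 = 9.53. The large-sample chi-square calculation gives 79.5% power at 54 and needs N = 55, so the stated 54 is reproduced to within one participant. The corresponding F calculation (df₂ = N − 3, λ = N f²) gives 77.0% at 54 and needs 58, or 60 when balanced. The planned 60 or more completers cover that, so the sample size is not the problem here.

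**One contrast, exactly.** In the saturated group-by-time model, the uncorrected sandwich variance of a group's mean change is Σ(d − d̄)²/n², which is (n − 1)/n times the unbiased value. At n = 20 that is 0.95. With normal data of equal variance, the pairwise statistic compared with 1.96 is a t variable on 38 df compared with 1.96 × √0.95 = 1.910. Its two-sided tail is 6.4%. For the two interoception groups combined against control, simulation gives 6.2%. A single three-way contrast gave 5.6% (1,200 runs).

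**Multi-df tests.** W = c′V⁻¹c, with V the uncorrected sandwich, was referred to chi-square on q df under the null (40,000 runs, Monte Carlo error about 0.15 points):

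| Test | q | 18 per group | 20 per group | 23 per group |
|---|---|---|---|---|
| Group × time | 2 | 7.7% | 7.3% | 7.1% |
| Group × time × cue, three listed body areas | 4 | 10.1% | 9.6% | 8.7% |
| Group × time × cue, no-cue added as fourth level | 6 | 13.2% | 12.0% | 11.1% |

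Cued against not cued (2 df) gives 7.7% at 20 per group. Repeat simulations at 20 per group gave 7.4–7.5%, 9.5–9.6% and 12.4–12.5% for the three rows. A fitted GEE with exchangeable working correlation (1,000–1,500 runs, so less precise) gave 8.1%, 10.0% and 12.4%. Log-normal data gave 7.2%, 9.1% and 11.6%.

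**Sensitivity, by assumption.** A reaction time exists only if the participant responds, so trial counts will differ between people. The documents give no response rates. With Beta-distributed rates assumed, a trial-level version using the protocol's trial counts gave 8.1–8.6%, 10.5–11.7% and 13.5–16.8% at 20 per group.

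**With a correction, 20 per group.** Kauermann-Carroll multiplies W by (n − 1)/n = 0.95; Mancl-DeRouen multiplies it by 0.95² = 0.9025. Let ν = N − 3 = 57.

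| Correction and reference | 2 df | 4 df | 6 df |
|---|---|---|---|
| Kauermann-Carroll, (ν − q + 1)W/(νq) against F(q, ν − q + 1) | 5.3% | 5.5% | 5.5% |
| Mancl-DeRouen, W/q against F(q, 57) | 5.0% | 5.7% | 6.9% |
| Kauermann-Carroll, W/q against F(q, 57) | 5.7% | 6.7% | 8.3% |
| Kauermann-Carroll, W against chi-square | 6.5% | 8.2% | 10.7% |

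The corrected variance alone is not enough. The reference distribution matters too.

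**The case against.** The strongest reply is that the article makes no commitment to uncorrected tests. It names GEE, interactions and a significance level. Variance estimators and denominator degrees of freedom are normally settled in an analysis plan, which is not shown, and with a correction the level is close to nominal. This stands, and it makes the point conditional. A reader might infer that the trial's 5% is in fact 7% and 13%. The documents do not support that, because no figure can be attached to an unstated estimator. The sentence about repeated measures and non-normality is also not false; it is silent on sample size.

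Second, a figure of about 13% for the cue test needs a single four-level cue factor, and even then 12.0% is the value at 20 per group. The Variables section lists a three-level or a two-level factor. This also stands.

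Third, hypotheses 1 and 2 for the spatial cueing task are mostly directed comparisons: groups pairwise, interoception combined against control, and a matching cue in one group. Tested as single-df contrasts, they run at about 5.6–6.4%, a mild excess. This stands, and the larger figures apply only to omnibus tests.

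Two further inferences go beyond the text. The predictor list does not specify a five-way interaction model. The drop-out allowance of 5–10 does not show outcome-related loss, so it gives no ground to call GEE biased here or to require a mixed model in its place.

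What survives is that the method, the interactions, the level and the number of clusters are all fixed in the article. The usual default inference for that combination exceeds the stated level.

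**Conclusion.** The point holds conditionally. With uncorrected robust Wald chi-square tests and 20 participants per group, type I error is about 7% for the 2-df group-by-time test. For the omnibus group-by-time-by-cue test it is about 10% with the three-level cue and about 8% for cued against not cued; about 12% arises only with an unlisted fourth level. Single-df contrasts run at about 6%.

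These figures assume equal groups, complete data, equal variances under the null and a saturated mean model. Unequal response counts would raise them somewhat. The excess is modest for the main test, material for the omnibus cue test, and almost free to remove. GEE itself remains a defensible choice.

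**What to change.** State in the analysis plan that:

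- the participant is the cluster;
- the sandwich variance carries a small-sample correction (Kauermann-Carroll or Mancl-DeRouen);
- single contrasts are referred to t, and multi-df tests to F, with degrees of freedom based on the number of participants. With Kauermann-Carroll, use the scaled F in the first line of the second table, since a plain F on 57 df leaves 6.7% on the 4-df test.

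If the plan not shown already says this, nothing further is needed.

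The cost is one sentence and slightly wider intervals. At 20 per group, for a single contrast on t with 57 df, the width ratio is √(20/19) × 2.002/1.960 = 1.026 × 1.022 = 1.05 with Kauermann-Carroll, and (20/19) × 1.022 = 1.08 with Mancl-DeRouen. No extra participants are required by this change.

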## Discussion

To our knowledge, this will be the first project to investigate whether emotion presents as a localised phenomenon in the body and, further, whether awareness of an active location can be trained, with a view to improving emotion regulation. The extension of these empirical studies to encompass a conceptual analysis of how the findings may relate to theories of suicide will be additionally novel.

Although there is a low chance of harm coming to any of the participants from taking part in the project, particularly due to the decision to recruit only healthy participants at this stage, there will be several processes of reducing risk. Firstly, given that participants will be responding to questionnaires containing reference to emotional sensitivity and health status, there is a small possibility of a negative reaction to these. Further, during the intervention, some participants will be asked to attend to their physiological activity, which is consistent with some meditative practices. Although there are no studies reporting any complications with interoception specifically, the meditative overlap may lead to some of the difficulties that have occasionally been reported with some practices [97]. Also, during the laboratory tasks, participants will be exposed to standardised emotional stimuli designed to elicit strong emotional responses.

As a response to these risks, the screening procedures are in place to ensure that people experiencing psychological/psychiatric difficulties will be excluded from participation. This aims to reduce the possibility of a pre-existing condition that lowers the threshold for possible anxiety or stress in relation to the emotional stimuli, questionnaires, or undertaking meditation. Further, the contact email address for the lead researcher will be available to all participants, who will be encouraged to raise any concerns, bearing in mind that they will be undertaking a daily interoceptive practice so will have regular reminders of this support. Similarly, at various points throughout each laboratory session, participants will be asked if they have any concerns regarding the emotional content of any of the stimuli, or any other aspect of the procedures. Ultimately, any concerns raised by participants will be referred to the supervisory team, two of whom are registered clinicians in psychology/psychiatry. Further, a medical doctor linked to the project can provide guidance on physical health.

One key source of risk, identified at the time of developing the theoretical framework, will also be addressed using screening. Much of the literature on emotion regulation emphasises the critical importance of inhibition to prevent the individual from becoming overwhelmed (e.g. [98]). One of the more extreme cases of apparent *disinhibition* in relation to emotion and the body is “somatosensory amplification” and related constructs, such as “somatising”, “catastrophising”, and “hypochondria”. These are related to anxiety disorders and others, suggesting that increased interoception is not a realistic option for those affected by amplification of bodily signals. Hence, it would be important to exclude those experiencing amplification from participating in the project. Screening will be undertaken using the SSAS. The overall score on the SSAS is simply a sum of scores for each item (i.e. a maximum of 50 from 10 questions using a 5-point scale).

Whilst there is no established cut-off for high somatosensory amplification in the SSAS, some studies have indicated a score of around 30 to be potentially problematic. For example, Nakao and Barsky [99] indicate that the averages for healthy men and women are slightly below 30, with non-healthy averages somewhat over 30, including cross-culturally (i.e. Japan, Turkey, France, the USA). The standard deviations for these studies show a degree of overlap between healthy and hypochondriac groups, meaning that an unspecified number of healthy people will likely score over 30. In order to reflect these concerns, in the current protocol, the limit has been set at a maximum score of 35. Whilst higher than the suggestions in the literature, this will ensure that healthy individuals are not excluded whilst also ensuring that amplifiers at the higher end of the scale will be excluded. In combination with the other screening measures—given the aim to ensure that ultimately only healthy individuals will be recruited—this will limit any potential negative impact indicated by an SSAS score > 30.

However, somatosensory amplification may be an issue only for those who engage in the negative appraisal of bodily changes, rather than increased body awareness itself being problematic: physiological activation has been found to be no higher in those with somatosensory amplification than those without it (e.g. [100]). To disinhibit emotional sensations, then, does not necessitate catastrophe, unless one is already prone to cognitive “catastrophising”. Hence, increased interoceptive sensitivity may not, per se, present a risk to participants, although we have erred on the side of caution.

The findings of the studies will be disseminated by journal article publications, public availability of a PhD thesis, and by conference presentations.

